### Criteria for discontinuation

Every effort will be made to retain patients in the trial and to minimise withdrawals. Patients may request to be withdrawn from this study at any time. Intention to treat and "as treated" analyses will be performed.

### Data Collection

Data will be obtained from copies of the anaesthetic record, recovery room observation chart, PCA chart, ward observation chart and drug prescription chart. These charts will be reviewed after the first 48 hour post-operative period by a member of the research team. The researcher will be blinded to the anaesthetic technique used. All documentation relating to the study will be stored in an anonymised case report file unique to each patient. These case report files will be archived in a locked facility for a period of 10 years.

### Sample Size and Statistical Considerations

In the comparison of ultrasound guided fascia iliaca block with spinal opioid in patients undergoing primary hip replacement, we intend to compare an established technique in widespread practice (spinal morphine) with the less well investigated technique of ultrasound guided fascia iliaca block. The primary outcome of the study is 24 hour morphine consumption. This outcome is used commonly in trials of spinal opioid for hip arthroplasty surgery. Mean 24 hour morphine consumption after hip arthroplasty is reported to lie within the range 10 mg [6] to 30 mg [7] when using 0.1 mg intrathecal morphine. From our own audit data of patients receiving spinal opioid for hip arthroplasty over an 8 month period, mean 24 hour post-operative morphine consumption was 24.6 (SD 17.6) mg which lies within the reported range described above [6,7].

In order to calculate sample size, we used a method suggested for non-inferiority trials [23,24]. For this we made the following assumptions. Type 1 error (α) was set at 0.05; Type 2 error (β) at 0.8; and Z numbers based on one-tailed testing. We considered a difference between groups (δ*) of greater than 10 mg of morphine to be clinically significant. 10 mg of morphine equates to one subcutaneous dose of morphine commonly used in post-operative analgesia pain protocols [25].

The expected difference between the Control (spinal morphine) and Treatment (ultrasound guided fascia iliaca) groups (δ) is more difficult to estimate. To date, there is only one published trial looking at 24 hour post-operative morphine consumption after fascia iliaca block for hip arthroplasty, although this was performed with the landmark technique alone and did not employ ultrasound [13]. In this study, mean 24 hour post-operative morphine consumption in the fascia iliaca group was 23 mg. Therefore, there is a 1.6 mg difference between the mean 24 hour morphine consumption obtained from our audit data of patients receiving spinal morphine, and that obtained in a study looking at patients receiving fascia iliaca block for hip arthroplasty [13]. Thus, the number of patients required to adequately power this study is 108.

The null Hypothesis (H0) for this non-inferiority study is that the experimental treatment (ultrasound guided fascia iliaca block) is in fact inferior to the established treatment (spinal morphine) by more than the clinically significant amount (δ*). If H0 is rejected, the alternative hypothesis is that ultrasound guided fascia iliaca block is not inferior to IT opioid.

The study will be performed using both intention to treat and "as treated" analyses. In the intention to treat analysis, patients will be considered failures if they require general anaesthesia, or were unable to receive randomised treatment for any other reason. In the "as treated" analysis, only data from patients completing randomised treatment will be analysed.

Secondary data analyses will be carried out on all secondary outcomes. These will be compared between groups using t-test, and Mann-Whitney, or Chi-squared tests as appropriate.

It is anticipated that recruitment for this study will take between 12 and 18 months to complete if 1 to 2 patients are enrolled each week, using one surgeon to reduce surgical variability. Data collection for each patient will occur during the first 48 hours post-operatively and at a routine 6 week follow up appointment. No further follow up will be routinely arranged. Any patients requiring specific follow up will have this arranged on an individual basis.

We recognise that while this study is powered for the primary outcome, it is not powered for the secondary outcomes. However, the data we collect in this study will provide useful information for further studies looking specifically at these outcomes.

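### The type 2 error is printed as 0.8, which is 20% power; the sample size of 108 was most likely calculated with 80% power, so the label needs correcting and the size does not

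*Protocol article*

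**What the plan says.** All the relevant statements are in the protocol article under Sample Size and Statistical Considerations. The error rates are given as "Type 1 error (α) was set at 0.05" and "Type 2 error (β) at 0.8", with "Z numbers based on one-tailed testing". The margin is set by "We considered a difference between groups (δ*) of greater than 10 mg of morphine to be clinically significant". The control figures come from the centre's own audit of spinal opioid patients: "mean 24 hour post-operative morphine consumption was 24.6 (SD 17.6) mg". For the block, the article cites one published trial of the landmark technique, in which "mean 24 hour post-operative morphine consumption in the fascia iliaca group was 23 mg". It concludes that "there is a 1.6 mg difference between the mean 24 hour morphine consumption" in the two sources, and then: "Thus, the number of patients required to adequately power this study is 108".

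The end of the section repeats that the study is powered for its primary outcome, though not for the secondary ones. Nowhere does the article give power as 80% or β as 0.2, so nothing else in it corrects the printed value.

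**The concern.** In this trial β is the probability of failing to show non-inferiority when the block truly is non-inferior by the assumed amount. Setting it at 0.8 declares a trial that would miss a true result four times in five. That cannot stand beside a claim of adequate power.

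This is the only number the article gives for β or power, and it is one of the inputs from which 108 is said to follow. A reader who sees that 0.8 cannot be β has to infer both the intended β and how the expected difference entered the formula.

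**Working it through.** **Inputs, all from the sample size section.** One-sided α = 0.05, so z = 1.645. SD = 17.6 mg, from the audit and applied here to both arms. Margin δ* = 10 mg. Expected difference 24.6 − 23 = 1.6 mg. Stated total 108, with no dropout allowance mentioned. The article does not give the allocation ratio; 1:1 is assumed, so 54 per arm.

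**Formula.** n per arm = 2 × (z₁₋α + z₁₋β)² × SD² / (δ* − δ)², where δ is the excess morphine use assumed for the block. SD² = 309.76.

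**Reproducing the stated figure.** Take 0.8 as power (β = 0.2, z = 0.842) and δ = +1.6, so the distance is 10 − 1.6 = 8.4 mg:

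2 × (1.645 + 0.842)² × 309.76 / 8.4² = 54.28 per arm, or 108.57 in total unrounded. Rounding up in each arm gives 55, or 110 in total. The stated 108 is the unrounded total cut to a whole number.

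Power at 54 per arm: the standard error is 17.6 × √(2/54) = 3.387 mg. Then 8.4/3.387 − 1.645 = 0.835, which gives 79.8%.

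**Taking β = 0.8 as printed.** Now z₁₋β = −0.842:

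2 × (1.645 − 0.842)² × 309.76 / 8.4² = 5.66 per arm, or 6 rounded up and 12 in total. The stated size is nine times that (108/12).

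**How far this depends on the expected difference.** Totals after rounding up per arm, one-sided α 0.05:

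| Assumed δ (block minus spinal morphine) | Distance | β = 0.8 | β = 0.2 | β = 0.1 | Power at 54 per arm |
|---|---|---|---|---|---|
| +1.6 mg (against the block) | 8.4 mg | 12 | 110 (108.57 unrounded) | 152 | 79.8% |
| 0 | 10 mg | 8 | 78 | 108 (106.11 unrounded) | 90.5% |
| −1.6 mg (sign of the cited means) | 11.6 mg | 6 | 58 | 80 | 96.3% |

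The β = 0.8 column never comes near 108. If α were read as one-sided 0.025, the totals at 20% power would be 22, 16 and 12 for the same three rows. For β = 0.8 to give 54 per arm, the distance would have to be √(2 × 0.803² × 309.76 / 54) = 2.72 mg, an assumed disadvantage of about 7.3 mg. The article states no such figure.

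**The case against.** The strongest reply is that this is a slip of one symbol. The value 0.8 is the customary figure for power, the section says twice that the study is powered for its primary outcome, and nobody would read it as planning a trial of 12 patients. The arithmetic was evidently done with a sensible power, and recruitment, margin and analysis are untouched. All of this stands, and it limits the weight of the point. It does not make the printed value right, and it cannot be excused as detail left to a fuller document, because the article states the figure itself.

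Three stronger readings are tempting and are not supported.

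- *The trial has only 20% power, or 108 is wrong.* On the article's own inputs 54 per arm gives 79.8% to 96.3% power, depending on how the 1.6 mg is used.
- *108 can come only from β = 0.2.* With no expected difference and β = 0.1 the formula gives 53.05 per arm, which rounds up to 54 and exactly 108. The reading with β = 0.2 and 8.4 mg is likelier, because the text states the 1.6 mg immediately before drawing its conclusion, but it matches only if the total is not rounded up.
- *The power cannot be checked by a reader.* The remaining inputs are printed and the method is cited. Reading 0.8 as power and choosing how to handle δ is enough to recover 108.

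**Conclusion.** The printed type 2 error is wrong as it stands and conflicts with the section's own claim of adequate power. Taken literally it calls for 6 to 12 patients at one-sided 0.05, across the three ways of using the 1.6 mg, against 108 stated. The most natural explanation is that power was printed as β.

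That explanation rests on three assumptions: 1:1 allocation, a common SD of 17.6 mg, and the 1.6 mg taken as a disadvantage to the block. The last is not stated, and the cited means (23 mg for the block, 24.6 mg for spinal morphine) point the other way. The intended β is therefore probable rather than certain, and only the sponsor can confirm it. This is a mislabelled design parameter, not a failure of the design.

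**What to change.** Subject to the sponsor confirming that this was the calculation, replace the statement with: type 2 error (β) 0.2 (power 0.8). Add a clause saying that the 1.6 mg was taken as a disadvantage to the block, leaving a distance of 8.4 mg to the margin. If the sponsor's records show another calculation, such as β = 0.1 with no expected difference, print that β and that δ instead.

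The formula need not be printed, since the method is cited. The cost is one number and one clause. Sample size, recruitment, analysis and conduct do not change.

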### Adverse Event Reporting and Safety

All adverse events will be recorded and discussed at monthly safety meetings by at least 2 investigators. If clinically indicated, the nature of the anaesthetic administered in the study may be revealed. After assessment by the Principle Investigator, any serious adverse events (SAEs) and suspected unexpected serious adverse reactions (SUSARs) will be reported to the Pharmacovigilance Office in the Robertson Centre for Biostatistics in Glasgow. All SUSARs will be reported to the Medicines and Healthcare products Regulatory Agency (MHRA) by the Pharmacovigilance Office at the Robertson Centre for Biostatistics in Glasgow.

## Discussion

### Risk Benefit Assessment

We expect that all patients will benefit from this study in view of the high level of post-operative monitoring and follow up which will be employed. In order to achieve blinding and improve the validity of the study, a "sham" ultrasound guided fascia iliaca block will be performed in patients in the *Spinal Morphine Group*. These patients will therefore receive an injection of an inactive substance (sterile saline) into the groin. As no local anaesthetic is being used in the sham block, potential risks will include; discomfort on injection, bleeding or bruising at the puncture site and nerve damage. Nerve damage is rare with fascia iliaca blocks as the needle is not directed towards the nerves themselves, but rather to lie in a plane between muscle layers. In the patients receiving fascia iliaca block with local anaesthetic, the risks are as before with the addition of local anaesthetic toxicity, although a pre-determined safe dose of local anaesthetic is being used.

Patients in the *Spinal Morphine Group *will receive intrathecal morphine. Spinal opioids have been used since 1979 to provide pain control after surgery [26]. Due to its widespread international use, intrathecal morphine has been extensively investigated in this setting and spinal morphine in combination with systemic morphine is a commonly used post-operative regime for many surgical procedures including hip arthroplasty [27-29]. Low dose intrathecal morphine can provide adequate analgesia whilst minimising side-effects [6-8]. Such side-effects include; delayed respiratory depression, pruritus, post-operative nausea and vomiting and urinary retention [5,30-32]. Although respiratory depression is rare with low doses of intrathecal morphine, [33] it is potentially life-threatening. Furthermore, the concomitant use of systemic opioids for post-operative analgesia may add to this risk. Previous research has concluded that 100 micrograms of intrathecal morphine combines analgesic efficacy whilst minimising the side effect profile [6,8]. Reassuringly, in a dose-finding study of intrathecal morphine for hip and knee surgery, there was no increased incidence of respiratory depression or hypoxaemia in patients receiving up to 0.3 mg of intrathecal morphine. This included elderly patients who had also received "significant doses of PCA morphine" [7].

A recent meta-analysis of 1300 patients was unable to define whether the use of intrathecal morphine increased the risk of respiratory depression [33]. Studies investigating the use of intrathecal opioid are generally not adequately powered to detect the incidence of respiratory depression. However, it is believed that lower doses result in a reduced risk [6-8,28,33,34]. A recent trial of 1915 patients receiving 0.15 mg of intrathecal morphine for Caesarean section found the incidence of a respiratory rate of less than 10 breaths per minute to be 0.26% and the need for naloxone 0.052% [34]. However, there is no evidence that there is an effective dose of intrathecal morphine that would completely preclude the occurrence of respiratory depression. An accurate estimate of the incidence of this complication would therefore require a trial containing very large numbers of patients and is impractical to undertake. In keeping with other investigators, we can not accurately predict the incidence of respiratory depression that may occur after the use of low dose intrathecal opioid and PCA morphine.

In the planning of this study, a number of measures have been employed to reduce this potential risk. These include; the utilisation of the lowest possible effective dose of intrathecal morphine (0.1 mg), the use of specific monitoring charts to ensure that the patient is monitored on an hourly basis, delivery of supplemental oxygen whilst receiving morphine via the PCA device, and the use of clear protocols to be followed by nursing staff in the management of adverse events. All nursing staff involved in post-operative patient care are competent and experienced in the management of patients who have received intrathecal and systemic morphine, and are trained in the necessary monitoring procedures.

Both spinal anaesthesia and peripheral nerve blockade are commonly performed for hip arthroplasty in the United Kingdom. Any possible risks must be weighed up against the risks of a general anaesthetic. Any adverse events relating to each of the procedures will be recorded by staff performing the study and any necessary investigations, treatment or follow up arranged thereafter.
